#### Video meeting for social network assessment

2.9.3

An online video call will be scheduled with participants in the mastectomy or voice training groups in which they will complete the *social network task* in the same week as their questionnaire completion. As with the GAHT group, participants will complete the tasks independently but will be able to ask questions to the research team member if needed. Each video meeting with the research team is estimated to take around 20 min.

### Measures

2.10

See Supplementary Table 1 for a full list of all study constructs, with corresponding instruments and references, and Fig. 4 for the placement of these constructs within the proposed conceptual model. We selected the questionnaires and instruments based on construct alignment (i.e., alignment with the construct we want to measure), face validity of the items, and instrument validation (i.e., has the questionnaire been previously validated?). The full questionnaires for each group and time point can also be found on the study OSF page (osf.io/zjkhv/).

#### Demographics and covariates

2.10.1

Participants will complete a series of demographics and potential covariates. At baseline and several follow-up timepoints, we will assess characteristics which enable us to conduct intersectional analyses, including but not limited to *age, gender, sexual and romantic orientation, socioeconomic status, migration background and ethnicity, education, mental healthcare, autism symptoms,* and *autism diagnosis status.*

#### Social stigma

2.10.2

To measure social stigma, we will use three measures assessing factors related to social stigma (and resilience), including *social gender affirmation*, *TGD minority stress*, and *sexual objectification*. In selecting these outcomes, we opted to include both positive (e.g., gender affirmation) and negative (e.g., minority stress) factors, as well as relevant constructs proposed by the LEE group (e.g., sexual objectification; [14]).

#### Gender congruence

2.10.3

We opt to use four measures assessing different aspects of gender congruence, including *gender congruence*, *gender euphoria*, *appearance satisfaction*, and *body appreciation*. Additionally, participants in the mastectomy control group will also complete a measure of *chest and nipple satisfaction,* as well as measures assessing *body expectations* at baseline and *effects of body image on life* at every timepoint. Participants in the voice training group will complete a measure of *voice satisfaction*.

#### Biological factors

2.10.4

To examine possible biological factors in the GAHT group, we will collect *serum hormone levels*, which are measured as part of routine clinical practice, in the GAHT group; we will ask participants about their *form and dosage of GAHT* to determine possible dosage- or administration-dependent effects of GAHT.

#### Psychosocial functioning

2.10.5

To measure psychosocial functioning, we opt to use measures assessing three facets of psychosocial functioning: self-, interpersonal-, and emotional-functioning. Participants in the GAHT group will additionally complete behavioral measures assessing *implicit gender associations*, *emotional inhibition, interpersonal trust,* and *self-control*, which will enable us to triangulate questionnaire data with behavioral tasks for more robust conclusions.

#### Social health

2.10.6

We will examine social health using both global measures of social health and nuanced evaluation of personal social networks. We will assess participant's *social networks* using a sociogram, as illustrated in Fig. 5, which captures the social connections between one person (the “ego”) and their social contacts (“alters”), as well as the connections between alters in the network. Best practices and recommendations for eliciting high quality network data (e.g., Ref. [23,24]) were followed in design and measurement decisions. Participants will first be asked to nominate up to 20 people that are in their social network. They will then be shown three concentric circles and asked to imagine themselves at the middle of the circles and to place each alter in the circle based on their closeness to the self and how close the alters are to each other. Participants will then complete measures assessing alter properties (e.g., *age, gender, relationship type, interaction frequency*), ego-alter properties (e.g., *support of transition, relationship satisfaction, conflict*), and alter-alter properties (i.e., *presence and quality of relationship*).

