#### Research question 3: how do social networks change after starting gender-affirming treatment, and do these changes influence outcomes of gender-affirming care?

2.1.3

Third, we aim to assess the dynamic relationships between social networks and gender-affirming care. We will investigate changes in social networks after starting gender-affirming treatment, including structural changes (e.g., number of people in social network, reported closeness to others, ties between social network members) as well as functional changes (e.g., relationship quality, perceived support of gender and transition), as well as potential effects of networks on care-related outcomes.

We hypothesize that after starting gender-affirming treatment, participants will report changes in social networks in line with improved social health, possibly reporting, for example, decreases in low-quality contacts (e.g., unsatisfying or unaffirming relationships) and increases in high-quality contacts (e.g., satisfying and affirming relationships), an increase in the proportion of social network members who are also TGD (or members of the LGBTQ + community) and/or who show higher rates of support for one's gender and transition.

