**Fig. 5 fig5:**
[figure not shown]
Example of personal social network assessment and related questions, as administered in Network Canvas.

To answer RQ 3, i.e., changes in social networks after starting gender-affirming treatments, we will examine various network properties at baseline and over the course of transition (e.g., number or proportion of supportive others compared to unsupportive others; the presence of TGD people in the network; the density of the network), as well as how baseline network characteristics (or changes in these) might predict treatment-related outcomes (e.g., life satisfaction). Further, we will explore whether there are differences in these network properties between the treatment groups.

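### For participants at or near the 20-name limit, network size is censored and a fall in low-quality contacts cannot be told apart from displacement by new contacts

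*Protocol article*

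**What the plan says.** Protocol article, section 2.10.6 (Social health), on the sociogram task: "Participants will first be asked to nominate up to 20 people that are in their social network". Participants place these people by closeness and rate each one (for example on support of transition, relationship satisfaction and conflict). They also report which of them know each other. The section says in general terms that recommended practice for network data was followed. It says nothing specific about people who reach the limit.

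Section 2.1.3 (Research question 3) lists as structural changes of interest "number of people in social network, reported closeness to others, ties between social network members". Its hypothesis is that "participants will report changes in social networks in line with improved social health, possibly reporting, for example, decreases in low-quality contacts", paired with "increases in high-quality contacts (e.g., satisfying and affirming relationships" and with "an increase in the proportion of social network members who are also TGD".

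Section 2.11.1 (Planned analyses, the RQ3 paragraph after Fig. 5) plans to follow properties such as "number or proportion of supportive others compared to unsupportive others", the presence of TGD people and network density. It also plans to relate baseline networks or their changes to treatment-related outcomes, and to explore differences between treatment groups.

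**The concern.** A list that stops at 20 cannot show growth beyond 20, so change in network size is pulled toward zero for anyone close to the limit. The same list supplies the contact counts. A person with a full list who gains affirming contacts has to leave someone off. If the people left off tend to be the less satisfying ones, the recorded number of low-quality contacts falls although every relationship continues. That error runs in the direction of one of the expected RQ3 patterns and grows with the true gain in contacts.

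Readers could then be told that people shed unsupportive contacts after starting treatment when, for some of them, the list had only filled up. If the share of participants at the limit differs between the GAHT, mastectomy and voice training groups, the group comparison of network properties is affected too.

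An analysis plan can model size as censored. It cannot recover whether an unlisted person is still a contact; that has to be asked when the data are collected.

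**Working it through.** There is no figure in the article to reproduce: it states no expected network size and no share of participants likely to reach 20. From the document come the limit of 20, the 150 GAHT participants and the 30% loss to follow-up (section 2.12). Everything else below is an assumption.

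**Step 1: exact counting.** Suppose no tie is lost and high-quality people are named first. With H high-quality and L low-quality contacts, named high = min(H, 20) and named low = min(L, 20 − named high).

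| True contacts at baseline | New high-quality | Named at baseline (high, low) | Named at follow-up (high, low) | True low-quality | True size |
|---|---|---|---|---|---|
| 10 (4 low) | 2 | 6, 4 | 8, 4 | 4 | 12 |
| 18 (4 low) | 2 | 14, 4 | 16, 4 | 4 | 20 |
| 19 (4 low) | 2 | 15, 4 | 17, 3 | 4 | 21 |
| 20 (5 low) | 2 | 15, 5 | 17, 3 | 5 | 22 |

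In the last row the recorded low-quality count drops from 5 to 3 and recorded size stays at 20, while the truth is 5 and 22. Where the true total stays at 20 or below, nothing is distorted.

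**Step 2: average size of the effect.** Simulation of 300,000 people per scenario. Assumptions: negative-binomial true size, 30% of baseline contacts low quality, Poisson number of new high-quality contacts, none lost. The true change in low-quality contacts is 0 throughout.

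| Mean size (SD) | Mean gain | Observed growth | Low-quality count, high-quality named first | Low-quality count, random naming |
|---|---|---|---|---|
| 8 (4) | 2 | 1.97 | falls 0.03 from 2.4 | falls 0.01 |
| 10 (4.5) | 2 | 1.91 | falls 0.09 from 2.9 | falls 0.02 |
| 12 (5) | 2 | 1.78 | falls 0.19 from 3.4 | falls 0.05 |
| 12 (5) | 4 | 3.4 | 3.40 to 2.91 (−0.49) | 3.53 to 3.40 (−0.13) |
| 15 (6) | 4 | 2.7 | 3.78 to 2.87 (−0.91) | 4.26 to 3.99 (−0.27) |
| 20 (8) | 4 | 1.7 | 3.47 to 2.20 (−1.27) | 5.05 to 4.58 (−0.47) |

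As shares of the baseline count with high-quality people named first: 0.91 / 3.78 = 24% at mean 15 and 1.27 / 3.47 = 37% at mean 20. At mean 8 the share is 0.03 / 2.4, about 1%. The share at the limit at baseline is 8%, 21% and 48% for means 12, 15 and 20.

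**Step 3: could a test pick it up?** Separate simulation: 150 × 0.70 = 105 people, 400 repetitions, paired t-test at two-sided 0.05 counting significant falls only. Assumptions: 25% low-quality contacts, a mean of 2 new contacts, none lost.

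| At the limit at baseline | False fall, lowest quality dropped first | False fall, random dropping |
|---|---|---|
| 0.2% | 0.00 | 0.00 |
| about 1.5% | 0.07 | 0.01 |
| 5% | 0.69 | 0.12 |
| 24% | 1.00 | 0.40 |
| 47% | 1.00 | 0.47 |

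With no new contacts the rate is 0.00 to 0.04 in every scenario. These probabilities lean high: the simulated low-quality count changes for no reason other than the limit, so even a small average shift (0.11 contacts in the 5% row, lowest quality dropped first) stands out. Ordinary variation between waves would lower them. They show that a modest share at the limit can matter, not how often it would.

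**The case against.** **The hypothesis.** A reader might infer that the limit can by itself confirm the main RQ3 hypothesis when nothing has changed. The article does not support that. The hypothesis is change consistent with better social health; fewer low-quality contacts is one illustration, introduced as a possibility. In the displacement scenario the gain in high-quality contacts is real, so the broader hypothesis would be partly true. A falling proportion of unsupportive contacts would also be real, because adding affirming contacts lowers it with or without a limit. Without new contacts, or some shift in who is named, the limit produces no meaningful fall. All of this stands.

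**The magnitude.** It rests on network sizes that the article does not give. Small networks, and gains of 2 rather than 4, bring the effect close to nil. This stands too, and is why a range is reported.

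**The design.** The limit contains burden: 20 names already give 20 × 19 / 2 = 190 possible pairs, in a video meeting planned at about 20 minutes (section 2.9.3). Each contact is rated individually, global social-health measures accompany the task, and the sample size was set for RQ1. These are good reasons to keep the limit, and the fix keeps it. They do not show whether an unlisted person is still a contact.

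**The missing detail.** Treatment of censored values belongs to an analysis plan, and the study materials on OSF, which are not shown, may contain a check on earlier names. So its absence cannot be asserted. What remains is a property of the stated data collection: unless the status of unrepeated names is asked, no later analysis can supply it.

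**Conclusion.** The point holds in a limited form. Nominated network size, an RQ3 outcome, is right-censored at 20. For people at or near that number, a fall in the count of low-quality contacts cannot be separated from displacement by newly gained ones. People who stay below the limit are unaffected.

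The size is unknown and spans a wide range under the stated assumptions: negligible when mean networks are about 8 to 10 with few people at the limit, and substantial at means of 15 to 20 with 4 new contacts. It also depends on whom people leave off: at mean 15 the apparent fall is about 0.9 if high-quality people are named first and about 0.3 if naming is random. The RQ3 hypothesis as a whole is not undermined. This is an inexpensive improvement to data collection, worth making because the missing information cannot be reconstructed afterwards.

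**What to change.** 1. Keep the 20-name limit for the detailed ratings.
2. At each wave of the network task, add one item asking how many people are in the network in total, and use it for the size outcome. Alternatively, analyse nominated size as right-censored at 20.
3. At each follow-up, after free nomination, show the people named previously but not repeated and ask whether contact continues. Count a tie as lost only if the participant says it ended. Asking afterwards leaves the free nomination uninfluenced.
4. Report the share of participants at 20 names per wave and per treatment group, so that readers can see whether the issue matters in these data.
5. Repeat the contact-count analyses among participants below the limit, as a sensitivity analysis only. Excluding people by follow-up network size conditions on the outcome, so this should not replace the main analysis.

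Cost: a few minutes per wave, a change to the custom-built network interface, and one extra analysis. If the study materials already include a check of earlier names, only items 2, 4 and 5 remain.

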### Statistical analyses

2.11

#### Planned analyses

2.11.1

To address RQ1, i.e., effects of GAHT on social health and the mediating role of psychosocial functioning, we will conduct a longitudinal mediation analysis using multilevel models in which we examine the effects of GAHT on social health and the possible mediating role of self-, emotional-, or interpersonal-functioning on this association. In this analysis, we will only include participants who started GAHT. This analysis is theory-informed and tests our a priori hypothesis, which is that social health improves after starting GAHT due to changes in aspects of psychosocial functioning. The power analysis and sample size estimate for the study were based on this first RQ1 analysis. To complement these hypothesis-driven primary analyses, we will conduct additional analyses in which we examine associations between different aspects of psychosocial functioning and social health, and in which we also stratify analyses by GAHT types (i.e., masculinizing and feminizing GAHT).

To answer RQ2, i.e., differences between a biological, systemic gender-affirming treatment (i.e., GAHT) and non-systemic gender-affirming treatments (i.e., mastectomies and voice training), we will further examine changes in the aforementioned “black box”, i.e., the connection between gender-affirming treatment and changes in psychosocial functioning. To do so, we will conduct a second longitudinal mediation analysis using data from all groups, analyzing changes in the different facets of psychosocial functioning after participants start gender-affirming treatment and the possible mediating roles of social stigma, gender congruence, and biological factors. In this analysis, we will also account for the type of gender-affirming treatment as visualized in Fig. 2, meaning this analysis will offer group-level insights into the different effects of GAHT, voice training, and mastectomy.

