There is evidence of existing disparities in social health for TGD compared to cisgender people across the life course, including greater levels of family dysfunction [8], loneliness (e.g. Ref. [9]), and romantic relationship difficulties [10]. Unfortunately, research on TGD people's social networks (e.g., network size and density, relationship characteristics) and effects of gender-affirming care on social health is still scarce. Strong and supportive social relationships do lead to greater likelihood of accessing care and better outcomes of care for the individual [11], but medical interventions can also have social consequences [6]. GAHT has systemic effects on the body, including effects on the brain [12], and TGD people who start GAHT show changes in emotionality and self-regulation [[13], [14], [15]], which could impact social relationships.

Therefore, a primary way in which GAHT may affect social health is through its influence on psychosocial functioning. Although this term is used in diverse ways across the literature, here we use psychosocial functioning to refer to self- (e.g., self-control), interpersonal- (e.g., interpersonal trust) and emotional-functioning (e.g., emotion regulation). In preparation for this project, we systematically reviewed literature pertaining to changes in psychosocial functioning after GAHT, identifying 46 studies [13]. Our review highlighted relatively consistent evidence for reductions in psychological distress and depressive symptoms after GAHT, but more mixed and inconclusive findings for other outcomes, such as general and social anxiety symptoms, emotion expression, and self-control. These studies did not consistently or regularly account for important potential confounders (e.g., body image, sexuality) or incorporate control groups to bolster causal inference. Moreover, the temporal nature of changes in psychosocial functioning, including how they may fluctuate or shift from one timepoint to another, has not been adequately considered.

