#### Research question 2: which effects of gender-affirming treatment on psychosocial functioning and social health are unique to the GAHT group, possibly due to biological systemic effects of hormones?

2.1.2

Second, we aim to differentiate the effects of GAHT from other forms of gender-affirming care (without systemic biological effects) in order to best isolate a potential biological pathway through which GAHT affects psychosocial functioning. We do so by including TGD people starting gender-affirming voice training or undergoing a gender-affirming mastectomy as comparison groups, allowing an assessment of the differences between non-hormonal and hormonal forms of gender-affirming treatment to disentangle effects of biological factors, social stigma, and gender congruence on psychosocial functioning and consequently social health outcomes.

We hypothesize that there will be differences and similarities in the effects of hormonal and non-hormonal gender-affirming treatments on psychosocial outcomes and these will be explained by differences/similarities in social stigma, gender congruence, and biological pathways.

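### RQ2 asks about social health, but no planned analysis compares global social health between arms: the all-group model stops at psychosocial functioning, and RQ1 uses GAHT starters only

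*Protocol article*

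**What the plan says.** Section 2.1.2 of the protocol article poses RQ2 as "which effects of gender-affirming treatment on psychosocial functioning and social health are unique to the GAHT group". Its text gives the voice-training and mastectomy arms the task of separating the pathways to psychosocial functioning and, through it, to social health.

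Section 2.11.1 then sets out the analyses:

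- **RQ1** is a longitudinal multilevel mediation model with social health as outcome. Its hypothesis is that "social health improves after starting GAHT due to changes in aspects of psychosocial functioning". On the population it says: "In this analysis, we will only include participants who started GAHT". The supplementary RQ1 analyses are associations and a stratification by GAHT type; neither involves the other arms.
- **RQ2** is a second mediation model, "using data from all groups, analyzing changes in the different facets of psychosocial functioning after participants start gender-affirming treatment". It targets "the connection between gender-affirming treatment and changes in psychosocial functioning", with social stigma, gender congruence and biological factors as mediators. Social health is not named as an outcome.
- **RQ3** examines personal networks and adds: "Further, we will explore whether there are differences in these network properties between the treatment groups".

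Section 2.10.6 measures social health in two ways, by global measures and by personal networks. Section 2.9 schedules questionnaires in every arm at baseline and at 3, 6, 12 and 24 months. Section 3.1 calls the design quasi-experimental because of the active control groups. Section 3.2 says the study will better isolate biological effects of GAHT on social health as well as on psychosocial functioning.

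**The concern.** The RQ2 question and the RQ2 analysis do not match. The question names two outcomes and the model has one. This is not detail left out of a condensed article, because section 2.11.1 states the population and the outcome of each analysis.

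Global social health is then analysed only in RQ1. There every participant is untreated at baseline and treated afterwards, so treatment status coincides with time since start. Secular change, regression to the mean, repeated questionnaires, social transition and the routine mental-health appointments that section 2.7.1 describes for the GAHT group all enter the same coefficient as GAHT. Statements about an effect of GAHT on global social health would rest on a time trend, although two comparison arms are followed on the same schedule.

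**Working it through.** **1. Which analysis covers which outcome (section 2.11.1)**

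| Outcome | Within GAHT | Between arms |
|---|---|---|
| Psychosocial functioning | RQ1 (as mediator) | RQ2 all-group model |
| Network properties | RQ3 | RQ3, exploratory |
| Global social health | RQ1 | none planned |

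Only the last row lacks a between-arm comparison.

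**2. The plan's own figures (section 2.12)**

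The plan needs 100 GAHT participants and assumes about 30% loss: 100 / (1 − 0.30) = 143. The stated 150 is a rounding up and leaves 150 × 0.70 = 105. The stated power of 0.80 cannot be reproduced exactly, because the method lies in a cited source and alpha is not stated. A joint-significance approximation that uses 0.26 and 0.39 as coefficients gives 0.72 with N = 100 and one observation each. It gives 0.88 with an effective N of 100 × 5 / (1 + 4 × 0.6) = 147. These bracket 0.80, but other readings of the two d values range from 0.13 to 1.00. The power is for mediation within the GAHT group. The point made here does not depend on it.

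**3. Illustration: drift in the single-arm contrast**

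Assumptions:
- no GAHT effect on social health;
- baseline compared with the mean of four follow-ups;
- two-sided alpha 0.05;
- total SD 1 and ICC 0.6, which section 2.12 states for psychosocial functioning and which is applied here to social health;
- no between-person variation in change;
- 105 completers.

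SE = sqrt[(1 − 0.6) × (1 + 1/4) / 105] = sqrt(0.5 / 105) = 0.069.

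P(reject) = Φ(drift/SE − 1.96) + Φ(−drift/SE − 1.96):

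| Assumed drift (SD) | n = 100 | n = 105 | n = 150 |
|---|---|---|---|
| 0 | 0.05 | 0.05 | 0.05 |
| 0.10 | 0.29 | 0.31 | 0.41 |
| 0.15 | 0.56 | 0.59 | 0.74 |
| 0.20 | 0.81 | 0.83 | 0.93 |

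The documents give no drift. All the values tried are below the 0.26 that section 2.12 assumes for GAHT's effect on psychosocial functioning.

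**4. The same contrast between arms**

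With 105 in GAHT and 105 pooled comparators, SE = sqrt(2 × 0.5 / 105) = 0.098. In 4,000 simulated studies per setting, with a drift of 0, 0.10 or 0.20 SD shared by both arms, this contrast rejected in 4.7% to 5.2%.

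For a difference of 0.26, a size borrowed from the psychosocial assumption, power is Φ(0.26/0.098 − 1.96) = 0.76. At 150 against 150 it is 0.89. Power of 0.80 needs 2 × 0.5 × (1.96 + 0.84)² / 0.26², or 117 per arm. With a single follow-up visit at 105 against 105, power falls to 0.56 on the change score or 0.65 with ANCOVA.

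**The case against.** The strongest defence is that the split follows the theoretical model. Fig. 1's caption places psychosocial functioning between treatment and social health, so RQ2 tests the upstream link across arms and RQ1 the downstream link within GAHT. RQ1 is openly a within-person design, and its hypothesis speaks of improvement after starting GAHT. Further analyses may be preregistered (sections 2.11.2 and 2.14). This explains the design, but RQ2 as worded still names social health, and no stated analysis answers that part for the global measures.

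Some stronger readings are tempting, and the documents do not support them:

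- *Social health gets no controlled comparison at all.* Networks are one of its two components, and RQ3 explores them between arms.
- *The protocol repeats the fault it finds in earlier work.* The Introduction says that earlier studies did not consistently account for confounders "or incorporate control groups to bolster causal inference". That remark concerns studies of psychosocial functioning, and for that outcome RQ2 does use the comparison arms.
- *All of RQ1 is a time trend.* The path from psychosocial functioning to social health is not purely one. The plan also stratifies by GAHT type, and section 2.10.4 collects dose and serum levels. Exposure coding is not stated, so pre/post coding is an assumption.

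The objection to the size also stands in part. The rejection rates follow from chosen drifts and a borrowed ICC, and they concern a total-effect test, not the mediation test that was powered. Between-person variation in change would enlarge the SE and lower them.

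**Conclusion.** The point holds for the global social-health measures and should be fixed. RQ2 asks about social health and its model omits it. RQ1 alone cannot separate the total effect of GAHT on global social health, or the path from GAHT to psychosocial functioning, from change over time. This conclusion rests on the text and needs no numerical assumption.

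The 31%, 59% and 83% only illustrate how sensitive a single-arm contrast is to modest drift. They depend on every assumption listed with them and do not predict this study's error rate. A reader might also infer that a between-arm contrast would deliver the causal effect of GAHT. It would not. The comparators are active and non-randomised, so the contrast estimates GAHT relative to other treatments and removes only drift that the arms share. Regression to the mean and social transition may differ by arm. Section 2.9 ties baseline to treatment approval for the GAHT and mastectomy groups only.

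**What to change.** - Add global social health as an outcome of the RQ2 all-group model, as a treatment-by-time contrast. Keep baseline as one of the repeated measures, and give a baseline-adjusted version as a sensitivity analysis, because baseline adjustment can itself bias a comparison of non-randomised arms.
- Restrict the contrast to waves at which the measure is collected in all arms. Every arm has five questionnaire waves, but their length differs (70 or 40 minutes, section 2.9.1) and the instrument list is in a supplement not shown. The overlap has to be confirmed.
- In that contrast, censor comparison participants' data when they start GAHT. Sections 2.7.2 and 2.7.3 let them re-enter in the GAHT group and keep their prior data in the comparison group, so the model must also account for people who contribute to two arms.
- Describe the RQ1 result as change after starting GAHT, and rest GAHT-specific statements about global social health on the between-arm contrast.

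**Cost.** If the measures overlap as the schedule suggests, no new data are needed and the change is to the analysis plan. The contrast is less precise than pre/post change (SE 0.098 against 0.069 under the assumptions above). Its power of 0.76 at 105 against 105 is optimistic if comparators are lost to follow-up at a higher rate or move into GAHT. It complements RQ1 and does not replace it, since it does not estimate the total effect of GAHT.
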